### Assessment of Study Outcomes

#### Primary Outcome

Our primary outcome is the difference in change over time in perceived stress (baseline to week 12) between the groups. Perceived stress was measured using the self-reported Stress Indicator Questionnaire [42]. Total scores range from 73 to 365 points, with higher total scores indicating higher levels of perceived stress.

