#### Secondary Outcome

Our secondary outcome is the difference in the change of diet quality between the groups. Dietary intake was assessed using paper-based 3-day food records that were analyzed using Food Processor Nutrition Analysis Software, version 11.0.3 (ESHA Research). Participants were asked to enter information about all the food, beverages, and supplements they consumed over 3 days, with 2 of the days on a weekday and 1 of the days on a weekend day. Instructions on how to complete the food records were included at the beginning of the paper food record booklet. In addition, instructions on how to complete food records were provided in person with participants during their baseline visit.

Diet quality was estimated using the nutrient rich food (NRF) index version 9.3 [43,44]. This index calculates a nutrient density score based on the amount of nutrients per 100 kcal serving of an individual food item: saturated fat, sodium, total sugar, protein, fiber, iron, magnesium, calcium, potassium, and vitamins A, C, and D. The percent daily value was calculated for all the nutrients. The sum of the percent daily values of nutrients to limit (saturated fat, sodium, and total sugar) was subtracted from the sum of nutrients to encourage (protein, fiber, iron, magnesium, calcium, potassium, and vitamins A, C, and D) to obtain the NRF score for that food item.

Vitamin D was chosen to replace vitamin E because it has been identified as an important nutrient for encouraging [45,46]. For protein, the lower limit of 10% of calories from protein in a 2000-kcal diet was used based on the acceptable macronutrient distribution ranges [47]. The percent daily values used in this study were 20 g saturated fat, 2400 mg sodium, 100 g total sugar, 50 g protein, 25 g fiber, 14 mg iron, 420 mg magnesium, 1100 mg calcium, 4700 mg potassium, 1000 retinol equivalent vitamin A, 60 mg vitamin C, and 600 international unit vitamin D.

To limit the effect of fortified foods, percent daily values were capped at 100%. A low or negative NRF score indicates a low-nutrient–dense food, and a high or positive NRF score indicates greater nutrient density. The total score was calculated by averaging all individual food scores within a 3-day food record.

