### Statistical Analysis and Power and Sample Size Rationale

#### Statistical Analysis

Our analysis of the primary outcome will be based on an intention-to-treat analysis using inverse probability weighting. Our analysis of the secondary and exploratory outcomes will be based on per-protocol and intention-to-treat analyses using inverse probability weighting. The effects of intervention over time will also be investigated using a generalized estimating equation. SPSS 25 (IBM Corporation) statistical software will be used for the data analysis. Characteristic variables will be compared between the 2 treatment groups and between those that did and did not complete the study. Differential variables will be used as covariates in the statistical analyses. *P*<.05 will be considered statistically significant.

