#### Power and Sample Size

The sample size was calculated using G-Power software (version 3.1.9.2, Heinrich-Heine-Universität Düsseldorf) [59] and based on the perceived stress scale scores of distressed adults after an internet-based stress management intervention [60]. With effect sizes of 0.74, a level of significance of 5%, and statistical power of 95% (power=1-β=0.95), the number of participants required is 33. With an anticipated attrition rate of 20%, we aimed to recruit 100 participants and have 80 participants complete the intervention.

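### Baseline stress and baseline diet quality are adjusted for only if they are found to differ, which gives up precision in a comparison of change and makes the primary model data-dependent

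*Protocol article*

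**What the plan says.** Under Primary Outcome, the protocol article states: "Our primary outcome is the difference in change over time in perceived stress (baseline to week 12) between the groups". Under Secondary Outcome it states: "Our secondary outcome is the difference in the change of diet quality between the groups".

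Under Statistical Analysis, the primary method is given as follows: "Our analysis of the primary outcome will be based on an intention-to-treat analysis using inverse probability weighting". A second approach is added: "The effects of intervention over time will also be investigated using a generalized estimating equation". The terms of neither model are listed. The same paragraph says that characteristics will be compared between the two arms and between completers and non-completers, and then sets the rule for adjustment: "Differential variables will be used as covariates in the statistical analyses".

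Perceived stress is measured at baseline, week 6 and week 12, and food records are kept at baseline and week 12, so every baseline value needed is available.

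**The concern.** A baseline covariate is useful because it predicts the outcome, not because the arms happen to differ on it. Baseline stress can be expected to predict week-12 stress, and baseline NRF score to predict week-12 NRF score. Under the stated rule, each enters only if it is counted as a characteristic and is then found to differ.

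Two things follow.

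- **Precision.** When the arms look balanced, the effect is a difference in change without baseline adjustment. A change score subtracts the whole baseline value rather than the part that carries forward to week 12, so it is noisier than an adjusted comparison.
- **Prespecification.** The covariate set of the primary model is decided after the data have been inspected, and so is not fixed in advance.

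The additional generalized estimating equation does not clearly repair this. If it has a free group-by-time term, its week-12 contrast is again essentially a difference in changes.

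**Working it through.** **Inputs from the article**

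- Effect size 0.74, significance level 5%, power 95%, required number 33 (Power and Sample Size). The article does not say whether 0.74 is in SDs of the score or of the change, whether the test is one- or two-sided, or whether 33 is per arm or in total.
- Completers: 35 intervention, 45 control (Results).
- Randomised: 48 intervention, 49 control (Abstract, Methods).

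**Assumptions**

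- Two-sided test.
- Equal SD, s, at baseline and week 12.
- Baseline to week-12 correlation r, not given in the article, so taken over a range.

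**The plan's own figure.** A two-sided two-group t test at 0.74 and 95% power needs 49 per arm (48 by the normal approximation); one-sided, it needs 41 (40). Power with 33 per arm is 84% two-sided. The stated 33 is therefore not reproduced by a two-group comparison. That is a separate matter and does not decide this point. It means only that the power figures below are comparisons between two analyses and not a reconstruction of the plan's calculation.

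**Step 1: variance.**

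- Change score: Var = 2(1−r)s².
- Baseline-adjusted: Var = (1−r²)s² = (1−r)(1+r)s².
- Ratio, adjusted to change: (1+r)/2, which is below 1 for any r below 1.

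| r (assumed) | Variance ratio | Confidence interval narrower by 1−√ratio |
|---|---|---|
| 0.3 | 0.65 | 19% |
| 0.5 | 0.75 | 13% |
| 0.7 | 0.85 | 8% |
| 0.9 | 0.95 | 2.5% |

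**Step 2: the cost of estimating the slope.** With 80 completers the adjusted variance is multiplied by about 1+1/(80−4) = 1.013. A simulation at 35/45 with 20,000 runs gave ratios of 0.756, 0.864 and 0.965 at r = 0.5, 0.7 and 0.9, against 0.75, 0.85 and 0.95 from the formula. Break-even is where 1.013 × (1+r)/2 = 1, that is, r of about 0.97.

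**Step 3: power at 35/45.** Noncentral t with 78 degrees of freedom and noncentrality δ√(35×45/80), where δ is the effect divided by the SD of the quantity analysed. This is an unweighted completer approximation; the planned analysis is weighted.

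*If 0.74 is in raw-score SDs*, δ = 0.74/√(2(1−r)) for change and 0.74/√(1−r²) for the adjusted comparison:

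| r | δ, change | Power, change | δ, adjusted | Power, adjusted |
|---|---|---|---|---|
| 0.3 | 0.625 | 78.3% | 0.776 | 92.5% |
| 0.5 | 0.740 | 90.0% | 0.854 | 96.3% |
| 0.7 | 0.955 | 98.7% | 1.036 | 99.5% |

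*If 0.74 is in SDs of the change*, δ = 0.74 for change, giving 90.0% at every r. For the adjusted comparison δ = 0.74/√((1+r)/2), giving 98.0%, 96.3%, 94.0% and 91.4% at r = 0.3, 0.5, 0.7 and 0.9.

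**Step 4: what the stated rule does with these two analyses.** If baseline stress is found to differ, it is a covariate and the adjusted column applies. If it is not, nothing in the article puts it in the model and the change column applies. The choice between the columns rests on a comparison made after the data are in.

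**The case against.** The strongest reply is that the Primary Outcome sentence defines an outcome and not a model. Change analysed with baseline as a covariate gives the same treatment estimate as week-12 stress adjusted for baseline, and a journal article may leave model terms to an analysis plan that is not shown. This is correct. A reader might infer that the trial has committed itself to a simple, unadjusted comparison of change scores; the article nowhere says so. What remains is the covariate rule, which the article does state and which makes entry conditional on observed differences. That is a stated choice, not a detail left out.

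A second reply is that the rule already deals with a marked chance imbalance in baseline stress. It does, provided baseline stress counts as a characteristic. The loss falls in the other case, when the arms look alike and the covariate is left out although it would still explain outcome variance.

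A third reply is that the power gain is uncertain. This also stands. No correlation is given, the scale of 0.74 is not stated, and the figures ignore the weighting, whose weights may themselves use baseline stress. A reader might infer that adjustment restores the planned 95% power. In raw SD units that happens only for r of about 0.44 to 0.59: below this range the adjusted analysis stays under 95%, and above it the change score already reaches 95%.

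Finally, the Exploratory Outcomes section compares arms at the end of the 12 weeks as well as within groups over time, so the criticism of change scores does not describe those outcomes. One of them, physical activity, is also classified into categories.

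**Conclusion.** The point holds as a weakness of the stated covariate rule, applied to effects defined as change. Adjusting for baseline would cut the variance of the primary estimate by 35%, 25%, 15% or 5% at correlations of 0.3, 0.5, 0.7 or 0.9, assuming equal SDs at the two visits. The gain is useful at low to moderate correlation and small at high correlation; after the slope cost, adjustment loses only if r exceeds about 0.97.

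A reader might infer that the planned comparison is biased. The documents do not support that: under randomisation with complete data, a difference in change is unbiased, and the loss is one of efficiency and of a fixed model. Dropout is unequal (48−35 = 13 of 48 against 49−45 = 4 of 49), and the article's Limitations section recognises this, but that is a missing-data question which the weighting is meant to address. It is not a consequence of using change. The analysis is described in the future tense, so the change can still be made and should be.

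**What to change.** In Statistical Analysis, state that baseline perceived stress is a fixed covariate in the inverse-probability-weighted primary model whether or not the arms differ on it. State the same for baseline NRF score in the secondary analysis, and for the baseline value in the analysis of each continuous exploratory outcome. The covariate sentence should no longer decide whether these baseline values enter. The result can still be reported as an adjusted difference in change, so the outcome definitions need not be altered.

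The cost is a wording change and one degree of freedom, about 1% of variance with 80 completers. No new data are needed.

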#### Secondary Outcome

Our secondary outcome is the difference in the change of diet quality between the groups. Dietary intake was assessed using paper-based 3-day food records that were analyzed using Food Processor Nutrition Analysis Software, version 11.0.3 (ESHA Research). Participants were asked to enter information about all the food, beverages, and supplements they consumed over 3 days, with 2 of the days on a weekday and 1 of the days on a weekend day. Instructions on how to complete the food records were included at the beginning of the paper food record booklet. In addition, instructions on how to complete food records were provided in person with participants during their baseline visit.

Diet quality was estimated using the nutrient rich food (NRF) index version 9.3 [43,44]. This index calculates a nutrient density score based on the amount of nutrients per 100 kcal serving of an individual food item: saturated fat, sodium, total sugar, protein, fiber, iron, magnesium, calcium, potassium, and vitamins A, C, and D. The percent daily value was calculated for all the nutrients. The sum of the percent daily values of nutrients to limit (saturated fat, sodium, and total sugar) was subtracted from the sum of nutrients to encourage (protein, fiber, iron, magnesium, calcium, potassium, and vitamins A, C, and D) to obtain the NRF score for that food item.

Vitamin D was chosen to replace vitamin E because it has been identified as an important nutrient for encouraging [45,46]. For protein, the lower limit of 10% of calories from protein in a 2000-kcal diet was used based on the acceptable macronutrient distribution ranges [47]. The percent daily values used in this study were 20 g saturated fat, 2400 mg sodium, 100 g total sugar, 50 g protein, 25 g fiber, 14 mg iron, 420 mg magnesium, 1100 mg calcium, 4700 mg potassium, 1000 retinol equivalent vitamin A, 60 mg vitamin C, and 600 international unit vitamin D.

To limit the effect of fortified foods, percent daily values were capped at 100%. A low or negative NRF score indicates a low-nutrient–dense food, and a high or positive NRF score indicates greater nutrient density. The total score was calculated by averaging all individual food scores within a 3-day food record.

#### Exploratory Outcomes

The following exploratory outcomes were assessed and will be compared within groups (over time) and between groups at the end of the 12-week intervention period:

Body composition was assessed by a hand-to-foot multifrequency bioelectrical impedance analysis using the QuadScan 4000 (BodyStat). Participants were instructed to fast for 5 hours before testing (drinking water only) and to avoid intense physical activity for 12 hours. Immediately before testing, participants were instructed to remove their shoes, socks, and all metal accessories before lying in a supine position. Fat mass, fat-free mass, and total body water were estimated based on device-specific equations.Health-related quality of life was assessed using the self-administered 12-Item Short-Form Health Survey version 2 [48]. Physical and mental component summary scores on a scale of 0 to 100 were generated and interpreted against data from the general population of the United States. Higher scores indicate a greater quality of life [49], and a difference in summary scores between 3 and 5 points is considered clinically significant [50].Mindfulness was assessed using the self-administered Five Facet Mindfulness Questionnaire (FFMQ) [51]. The FFMQ contains 39 statements about 5 facets of mindfulness (observation, description, awareness actions, nonjudgment, and nonreactivity) that are rated and scored on a 5-point Likert-type scale from never true to always true. Construct validity of the FFMQ has been demonstrated [52].Mental well-being was measured using the self-administered Warwick-Edinburgh Mental Wellbeing Scale [53]. The 14 questions on aspects of mental well-being were assessed using a 5-point Likert scale that was used to score each question and summed for a total score, with a higher score indicating higher mental well-being [53].Physical activity was assessed using a validated, self-administered Godin-Shephard Leisure-Time Physical Activity Questionnaire [54]. The number of times in a typical week that strenuous, moderate, and mild or light activity longer than 15 minutes during free time was reported. A score was calculated based on the number of times per week multiplied by an intensity factor (9 for strenuous, 5 for moderate, and 3 for mild or light). On the basis of the total score, the amount of activity was classified as active, moderately active, or sedentary [55].

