**Objective:**

The primary aim of this 12-week randomized controlled trial is to assess the impact of a web-based wellness platform on perceived stress among first-year university students. The secondary aim is to assess the effects of the platform on diet quality. The exploratory objectives are to explore the effects of the platform on body composition, health-related quality of life, mindfulness, mental well-being, and physical activity.

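### The exploratory outcomes are to be compared within each group over time, which cannot show a platform effect; the between-group contrast should be named as the basis for any effect claim

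*Protocol article*

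**What the plan says.** The Objective in the Abstract sets the exploratory aim as to "explore the effects of the platform on body composition, health-related quality of life, mindfulness, mental well-being, and physical activity". Under Exploratory Outcomes, the article states that these outcomes "will be compared within groups (over time) and between groups at the end of the 12-week intervention period".

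The other outcomes are defined differently. Under Primary Outcome: "Our primary outcome is the difference in change over time in perceived stress (baseline to week 12) between the groups". Under Secondary Outcome: "Our secondary outcome is the difference in the change of diet quality between the groups".

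The Statistical Analysis section adds three relevant statements:

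- On the analysis sets: "Our analysis of the secondary and exploratory outcomes will be based on per-protocol and intention-to-treat analyses using inverse probability weighting".
- On the longitudinal model: "The effects of intervention over time will also be investigated using a generalized estimating equation". This sentence is not restricted to any outcome, and it names no group-by-time term.
- On covariates: "Differential variables will be used as covariates in the statistical analyses". These are characteristics found to differ between the groups, or between completers and non-completers.

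The significance criterion is P<.05; whether one- or two-sided is not stated.

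**The concern.** The aim is the effect of the platform, but one of the two comparisons listed for these outcomes is a before-after comparison inside each arm. Such a comparison measures everything that changed over 12 weeks, including whatever would have changed without the platform.

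The article gives its own reasons to expect such change. The Background reports a mean first-year weight gain of 1.36 kg (95% CI 1.15-1.57), a 0.7% rise in fat mass, and a worsening of diet and physical activity. The Intervention section treats the start of term, midterms and finals as distinct periods for students. Body composition and physical activity are among the exploratory outcomes.

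At stake is a reading such as improvement with the platform but not in controls, or worsening in controls only, when the two arms in fact moved alike. A second, smaller matter is precision: a week-12 comparison that does not use the baseline value discards information already collected.

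**Working it through.** The article states no figure for this comparison, so there is none to reproduce. The check measures how each comparison behaves when the platform does nothing.

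**Inputs from the article.** 48 and 49 students randomized (Abstract, Methods); 35 intervention and 45 control completers (Results); significance level 5% (Statistical Analysis).

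**Assumptions not in the article.** Two-sided testing; the same shift in both arms, expressed in SDs of the change score; baseline to week-12 correlation r of 0.5 or 0.7; no informative dropout; independent arms.

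**Step 1: within-arm test.** A paired t test with n students and a shift of δ SDs of change has noncentrality δ√n on n−1 degrees of freedom. For δ = 0.3:

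- Intervention: 0.3 × √35 = 1.77, giving a probability of significance of 0.407.
- Control: 0.3 × √45 = 2.01, giving 0.503.

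**Step 2: significant in one arm only.** Intervention only = p1(1 − p2); control only = p2(1 − p1).

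| Shared shift (SD of change) | p1 (n=35) | p2 (n=45) | Intervention only | Control only |
|---|---|---|---|---|
| 0.2 | 0.210 | 0.259 | 0.210 × 0.741 = 16% | 0.259 × 0.790 = 20% |
| 0.3 | 0.407 | 0.503 | 0.407 × 0.497 = 20% | 0.503 × 0.593 = 30% |
| 0.4 | 0.633 | 0.747 | 0.633 × 0.253 = 16% | 0.747 × 0.367 = 27% |

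If the shared drift is favourable, the intervention-only pattern flatters the platform. If it is adverse, the control-only pattern does. The two columns should therefore not be added to give a misleading-result rate.

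**Step 3: between-arm tests under the same null.** In 40,000 simulated trials with r = 0.5 and a shift of 0.3 SD (at r = 0.5 the SD of change equals the baseline SD), the week-12 between-group test rejected in 5.1% and the between-group test of change in 5.0%. The within-arm tests rejected in 40.7% (intervention) and 50.2% (control), in agreement with Step 1. A shift common to both arms cancels in either between-group test.

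**Step 4: precision of the week-12 contrast.** Relative to the baseline-adjusted contrast, an unadjusted week-12 difference has variance 1/(1 − r²):

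- r = 0.5: 1/(1 − 0.25) = 1.33, or 33% larger.
- r = 0.7: 1/(1 − 0.49) = 1.96, or 96% larger.

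In outcome SD units, the unadjusted standard error is √(1/35 + 1/45) = 0.225. The adjusted one is 0.225 × √(1 − r²), which is 0.195 at r = 0.5 and 0.161 at r = 0.7. The difference in change, 0.225 × √(2(1 − r)), gives 0.225 and 0.175.

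**The case against.** The strongest reply is that the Exploratory Outcomes sentence is not the whole plan. The GEE statement comes directly after the sentence on secondary and exploratory outcomes and is not restricted by outcome. The questionnaires have three time points and body composition has two, so a GEE can supply a between-group contrast over time. Weighted intention-to-treat analyses and covariate adjustment are also planned. An article may leave the model terms to an analysis plan that is not shown. This stands: a reader might infer that the exploratory outcomes will be analysed only by within-group tests and a raw week-12 comparison, and the article does not support that. Nor does it say that the week-12 comparison ignores baseline. Adjustment for baseline is simply not assured, because covariates are chosen according to whether they differ.

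A reader might also infer that term-time change could pass for a platform effect in the week-12 comparison. It cannot if it is common to both arms, because the control group is concurrent and randomized. What remains there is lost precision and uncorrected chance imbalance. Unequal attrition, 13/48 = 27% against 4/49 = 8%, is a separate threat to that comparison.

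Finally, nothing in the article says that significance in one arm and not the other will be taken as evidence of effect, and describing within-arm change is common practice. That also stands, and it limits the point to a risk of misreading. It does not remove the point: the within-group comparisons are stated, they sit beside a 5% significance criterion, and the article does not say which of the several results would support a claim of effect.

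**Conclusion.** The point holds as a minor one. The within-group comparisons stated for the exploratory outcomes do not address the stated aim, and they depart from the difference-in-change definition used for the primary and secondary outcomes.

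With no platform effect and a shared shift of 0.2 to 0.4 SD of change, the arm-specific tests give a one-arm-only result that flatters the platform in roughly 16% to 20% of trials if the drift is favourable, and 20% to 30% if it is adverse. These figures rest on the assumed shift, two-sided 5% testing and completer numbers. The article supports a direction of first-year change for some outcomes, but gives no 12-week shift on the SD scale. The sum of the two patterns at 0.3 SD, about 50%, might be read as the rate of false platform claims; it is not, because only one pattern favours the platform for a given drift.

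The week-12 between-group comparison is valid at its nominal level under shared drift. Its cost, if unadjusted, is a variance 33% to 96% larger at assumed correlations of 0.5 to 0.7. The primary and secondary conclusions are unaffected.

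**What to change.** Under Exploratory Outcomes, define each effect as the between-group difference at week 12 adjusted for the baseline value of that outcome, or as the group-by-time contrast from the GEE, reported as an estimate with a 95% CI. State that any claim of platform effect rests on that contrast. Report within-group changes descriptively, without hypothesis tests.

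Reconcile this with the Statistical Analysis section by saying which of the two contrasts is used for the exploratory outcomes, and by including the baseline value by design instead of only when it happens to differ between groups.

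The cost is a change of wording in the article and in any analysis plan. The analyses are described in the future tense, and the baseline and week-12 measurements are already scheduled, so no new data are needed.
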